**Any systemic**

1. Fever (defined as axillary temperature  37.5°C)
2. Drowsiness
3. Loss of appetite
4. Irritability/fussiness

## Unsolicited symptoms

Unsolicited symptom is defined as any adverse event (AE) reported in addition to those solicited during the clinical study. Also any “solicited” symptom with onset outside the specified period of follow-up for solicited symptoms will be reported as an unsolicited adverse event.

Unsolicited symptoms will be recorded from the first dose of vaccination to 30 days post third dose.

For the unsolicited symptoms, intensity will be assessed as follows:

| Mild | Easily tolerated by the subject, causing minimal discomfort and not interfering with everyday activities. |
| --- | --- |
| Moderate | Sufficiently discomforting to interfere with normal everyday activities. |
| Severe | Prevents normal, everyday activities. |

Outcome and causal relationship will be assess as described in section 13.4.2.3 and 13.4.2.4

# Secondary Evaluation Criteria: Immunogenicity

## Humoral Immune response

### Definition of the Criteria

The humoral response to vaccine antigens will be assessed by measuring by ELISA on D0, D28, D56, D84, D168 and D365, the levels of:

- IgG, (peptide et epitopes A, B, C and D)
- Isotypes IgG1, IgG2, IgG3, IgG4, (peptide)
- IgM (peptide)

### Parameters to be measured

The levels of IgG and IgM will be expressed as concentration (ng/ml). The sero-response will be defined in the post-vaccination to re-vaccination ratio. (D28/D0, D56/D0, D84/D0, D168/D0, and D365/D0).

Because of the prior natural exposure of trial subjects to Plasmodium falciparum and so to MSP3 antigen, it is anticipated that almost all participants will be sero-positive before vaccination occurs. Consequently, the sero-conversion rate, defined as the number of pre-vaccination sero-negative candidates having a concentration considered as positive after vaccination, will not be used.

### Method and Timing of Measurement

IgG concentrations against these antigens will be measured by ELISA (Enzyme Linked Immuno Sorbent Assay), which is an immuno-enzymatic technique that allows levels of blood antibodies to be measured.

Levels of IgG, IgM and isotypes IgG1, IgG2, IgG3 and IgG4 will be measured in the blood samples collected at visits V1, V17, V32, V33, V48, V49 and V50 i.e. on days D0, D28, D56, D112, D140, D252 and D365.

## Cellular Immune response

### Definition of the Criteria

The cellular immune response to vaccine’s antigens (peptide) will be assessed by measuring

The number of cells producing IFNγ by Elispot to MSP3-LSP and peptides MSP3 a,b,c,d before and four weeks after the second and the third injection.

### Method and timing

The ELISPOT will be done after in vitro stimulation with the peptide or peptide fragments (A, B, C and D) of peripheral blood mononuclear cells. The spots will be counted using ELISPOT reader.

The cells producing IFN-γ will be measured before (D0) and one month after the second (D56) and one month after the last injection (D84).

### Parameters to be measured

The cells producing IFNγ by Elispot expressed in number of spots /106 cells

## Exploratory assays: Functionality of immune response

The following exploratory tests shall be conducted to assess the functionality and quality of the induced immune responses:

### Native protein recognition on Merozoite

Mature schizont-stage proteins of *P. falciparum* (3D7 clone) will be extracted in Laemmli sample buffer, submitted to electrophoresis, and transferred to nitrocellulose as described9 Nitrocellulose strips will then be incubated with each sera and the reaction revealed.

The intensity of the reactivity was classified as negative, positive (+), or strongly positive (++).

### Antibody Dependant Cytophilic Inhibition

The functionality of IgG shall be assessed by using the Antibody Dependant Cytophilic Inhibition (ADCI) technique.

The assays for assessing functionality of immune responses will be done on samples obtained on the following days: D0, D84, D168 and D365

# Statistical Methods and Data Analysis

## Principal Objective

To assess the safety and reactogenicity of 3 doses of 30 µg and 15 µg MSP3 adjuvanted in aluminium hydroxide given at D0, D28 and D56 in healthy children aged 4-6 and 1-2 years old in Burkina Faso.

This will be achieved through conducting a randomised controlled trial. The trial will certainly be single blinded to the participants. Efforts will be made towards a double blind design in that concealment of vaccination will be ensured to all who will be involved in the objective assessment of trial endpoints.

## Sample size considerations

The trial sample size will be determined on the primary evaluation criteria, concerning the occurrence of systemic adverse events. The total sample size is calculated at 45 children to be distributed as shown in the table below:

| 1-2 Year Olds |
| --- |
| 15 receiving 15µg MSP 3 vaccine |
| 15 receiving 30µg MSP 3 vaccine |
| 15 receiving Hepatitis B vaccine |
| **45 Children in total** |

The hypothesis in absolute terms has the following assumptions considered:

The lost of follow-up or protocol deviation is anticipated to be no more than 10%. Therefore with a total sample size of 45, the study is adequately powered to show such a difference if the assumptions hold.

With 14 children completing follow-up in each MSP3 arm, the study will be have 90% power to detect at least one MSP3 vaccinated individual with a systemic reaction (or a serious adverse event) if the underlying risk of such an event is 15% or more. (The trial will have 80% power to detect at least one individual if the underlying risk is 11% or more and 95% power to detect at least one individual if the underlying risk is 19% or more).

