# Trial design and methodology

## Description and justification of design

The study is a single centre randomised controlled and blinded study (observer blind). It will be conducted at the CNRFP Vaccinology unit located in Balonghin. Children in the catchments area within the 1-2 years age group, whose parents consent will be screened to randomise 45 eligible participants.

Clinical, biological and immune response data gathered after vaccination with 15µg and 30µg MSP 3 LSP will be compared to:

- The children’s baseline data before vaccinations, and
- The post vaccination data of children in the control group.

Randomisation will ensure that the comparison groups are similar in relevant characteristics at baseline. The concealment of allocation before enrolment will further enforce the randomisation. Individuals who will make the assessment of the study end points will be completely blinded of the vaccine administered. This will ensure that there is no observer bias. Further, reporting or information bias will be minimised, because the recipients will also not be aware of which vaccine they have been administered. This is possible because the selected control vaccine has not been in routine use in this area, and has only now been recommended by the Ministry of Health. Cross over immunisation at the end of the trial will involve only those children who will received the study vaccine; they will be administered the control vaccine in the interest of public health benefits for them.

The schedule of vaccination at 0, 1 and 2 months has been adopted because it is suitable for the target group. The idea is to eventually deploy the vaccine through the expanded programme on immunisation should the vaccine become registered for public use. For the EPI age group, it is not only an efficient delivery mechanism, but they are also the most vulnerable group to malaria.

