## Statistical Methods

The analysis shall be descriptive; the sample size does not allow any comparison between groups. For categorical variables, frequency distributions, by vaccination group, will be presented. For continuous variables, box-whisker plots, medians, inter-quartile ranges and ranges will be presented by vaccination group.

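### Section 16.2 claims adequate power to show a difference that it never defines, section 16.4 says the sample size permits no group comparison, and the only figures given concern seeing one event in one arm

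*Protocol*

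**What the plan says.** Section 16.2 bases the size on the primary criterion, "concerning the occurrence of systemic adverse events". It allocates 45 children to three arms: "15 receiving 15µg MSP 3 vaccine", "15 receiving 30µg MSP 3 vaccine" and "15 receiving Hepatitis B vaccine".

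It then opens a hypothesis statement, "The hypothesis in absolute terms has the following assumptions considered". What follows is only an allowance of at most 10% for loss to follow-up or protocol deviation. From this it concludes that "the study is adequately powered to show such a difference if the assumptions hold".

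The next paragraph is quantified. With 14 completers per MSP3 arm, it gives 80, 90 and 95% power to detect at least one vaccinated child with a systemic reaction or serious adverse event, at underlying risks of 11, 15 and 19%.

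Section 16.4 says: "The analysis shall be descriptive; the sample size does not allow any comparison between groups". Section 4.1 lists the comparators for the MSP3 data as the children's own baseline and "The post vaccination data of children in the control group", and sets no test.

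**The concern.** A claim of power for a difference needs a difference, a reference risk, a significance level and a test. Section 16.2 gives none of these; an attrition allowance cannot supply them. The same 45 children are then said in 16.4 to be too few for any comparison. Both statements cannot stand.

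The placement adds to the problem. The single-arm probabilities come straight after the claim about a difference and also use the word power, so they can be taken as its support. They answer another question.

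This matters for the analysis one month after dose 3, which the synopsis ties to the safety Go/No-Go decision for phase 2b. A reader told that the trial is adequately powered could take similar event frequencies in the MSP3 and hepatitis B arms as evidence of no difference. The sample cannot support that inference.

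**Working it through.** **Inputs from section 16.2.** 15 children per arm; 14 completers per MSP3 arm; risks of 11, 15 and 19%; loss of at most 10%.

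**Assumed, because 16.2 gives no value.** Two-sided 5% Fisher exact test; control risk 0% or 5%, with higher values for range.

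**1. The plan's own figures.** The chance of at least one event among n children at risk p is 1 - (1 - p)^n. With n = 14:

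- p = 0.11: 1 - 0.89^14 = 80.4%
- p = 0.15: 1 - 0.85^14 = 89.7%
- p = 0.19: 1 - 0.81^14 = 94.8%

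These reproduce the stated 80, 90 and 95%. A 10% loss from 15 leaves 13.5, which the plan takes as 14; with 13 the results are 78.0, 87.9 and 93.5%. The formula uses one arm only. No control risk enters it, so it cannot be power for a difference.

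**2. Power for a difference at the same risks.** With 15 v 15 and no control events, Fisher's test first reaches p ≤ 0.05 at 5 MSP3 events (5 v 0, p = 0.042). With a control risk of 0%, power is therefore P(X ≥ 5) for X ~ Binomial(15, p). For a 5% control risk, the binomial probabilities of all rejecting tables are summed.

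| MSP3 risk | Control 0% | Control 5% |
|---|---|---|
| 11% | 2% | 1% |
| 15% | 6% | 3% |
| 19% | 14% | 7% |

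The pooled normal approximation, which is generous at these counts, gives 26, 34 and 42% against 0%, and 14 and 21% for 15 and 19% against 5%. All are well short of 80%.

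**3. What 15 v 15 could detect.** For 80% power by the same test, the MSP3 risk must reach about:

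| Control risk | MSP3 risk needed |
|---|---|
| 0% | 41% |
| 5% | 54% |
| 10% | 64% |
| 20% | 76% |

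Over control risks of 5-30%, a 30-point rise has 23-40% power and a 50-point rise has 68-82%. Pooling both MSP3 arms (30 v 15) lowers the MSP3 risks needed to about 33, 43, 52 and 66%.

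**4. Scale.** For 15% v 5% at 80% power, the pooled normal formula gives n per arm = [1.96√(2 × 0.10 × 0.90) + 0.842√(0.15 × 0.85 + 0.05 × 0.95)]² / 0.10² = (0.832 + 0.352)² / 0.01, or about 141 per arm against the 15 planned.

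**The case against.** The strongest reply is that this is leftover wording. Section 16.2 goes straight on to a complete and correct single-arm justification, 16.4 says plainly that the analysis is descriptive, and section 16.1 still mentions ages 4-6, which suggests retained text. A list of assumptions may also have been lost when the document was converted from PDF. The first part stands to this extent: the correction is to wording, and a descriptive phase 1b trial of 45 children is legitimate. A lost list would not rescue the sentence, because the conflict with 16.4 remains.

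Section 4.1 can fairly be read as promising descriptive comparison, so its conflict with 16.4 is one of wording.

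A reader might go further in three ways that the document does not support:

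- **That the control arm goes unused.** Section 16.4 presents results by vaccination group, and the safety monitoring reports tabulate events for both MSP3 and hepatitis B. Control data are used descriptively.
- **That the trial has almost no power for any difference.** Very large differences are detectable, as step 3 shows. Power is low at the risks 16.2 names.
- **That missing confidence intervals or adjusted antibody ratios are a defect.** The section on blinding promises a formal reporting and analysis plan, and such detail belongs there.

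Nor are the single-arm figures wrong: they reproduce and should stay.

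**Conclusion.** The power sentence in 16.2 is wrong as written. It claims a property that the protocol neither defines nor supports and that 16.4 denies. That conclusion needs no assumption beyond the text.

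The size of the gap does depend on the assumed test and control risks: about 1-14% power at 16.2's own risks against 0-5% in control, with 80% reached only near 41% v 0% or 54% v 5%. Another test or control risk would move these numbers; the normal approximation in step 2 shows by how much without changing the conclusion.

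The finding concerns a stated justification. It does not show that the trial is too small for its descriptive purpose, or that anyone has misread its results.

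**What to change.** - **Section 16.2:** delete the hypothesis sentence that leads to no hypothesis, and the sentence claiming adequate power for a difference. Keep the at-least-one-event figures, and name them as the basis for the size: the probability of observing one or more events among 14 children in a single MSP3 arm. Add that the trial is not powered for between-group differences.
- **Sections 4.1 and 16.4:** say in both that the comparison with control is descriptive, with no hypothesis tests. Add that similar frequencies at the Go/No-Go analysis are not evidence of no difference.
- **Optional, for the analysis plan:** exact intervals for proportions and differences, and baseline-adjusted antibody ratios.

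The cost is a few sentences and a less favourable statement of power. Sample size, arms and procedures stay as they are.

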## Data Set to be analysed

### Definition of Population

### Total Vaccinated Cohort

The Total Vaccinated Cohort will include all vaccinated subjects for whom data are available. Thus, the total analysis of safety will include all subjects with at least one vaccine administration documented and the total analysis of immunogenicity will include vaccinated subjects for whom data concerning immunogenicity endpoint measures are available. The Total Vaccinated Cohort analysis will be performed per treatment actually administered.

### According to protocol (ATP) cohort for analysis of safety

The ATP cohort for analysis of safety will include all evaluable subjects;

- who have received at least one dose of study vaccine according to their random assignment
- have sufficient data to perform an analysis of safety (at least one vaccine dose with safety follow-up)
- for whom administration site of study vaccine is per protocol
- who have not received a vaccine not specified or forbidden in the protocol and for whom elimination criteria were not applied
- for whom the randomization code has not been broken except for when unblinding has been carried out by the DSMB for Safety Analysis.
- who meet all eligibility criteria.

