### Method of blinding and breaking the study blind

Data pertaining to the trial will be collected in a double blinded (observer blinded) manner. “Double blinded (observer blinded)”in this context means that the vaccine recipient and their parent(s)/guardian(s) as well as those responsible for the evaluation of safety and immunogenicity endpoints will all be unaware the exact treatment, (MSP3 or Hepatitis B)given to the participant. The only study staff aware of the vaccine assignment for Hepatitis B or MSP3 will be those responsible for the storage and preparation of vaccines; these staff will play no other role in the study.

. Sealed envelopes labelled with the study ID number and containing the treatment allocated to each particular ID number will be provided to the investigator. The clinical investigator will only be allowed to open an envelope after ensuring that the child before him has met all eligibility criteria and has been given the study ID number. For each child, eligibility will have to be counter checked and signed by a second person before allocation of study ID number.

All envelopes will be retained to be checked by the clinical monitor.

The local safety monitor who is independent from the study team will also be provided a sealed randomisation list corresponding to each group. In total, 2 sealed randomisation list will be provided. If deemed necessary for reasons such as safety, the Local Safety Monitor in Ouagadougou as well as AMANET Central Safety will unblind the specific enrolled subject without revealing the study blind to the investigators.

As part of the safety monitoring plan, safety reports will be produced at 5 timepoints in the trial. An independent statistician will analyze the data, thereby maintaining the blind of the investigator group.

A formal reporting and analysis plan (RAP) will be developed. Once the study is completed and the database locked. AMANET will be responsible for initiating the execution of the statistical analysis plan in collaboration with the investigator team and breaking the blind.

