### Local Safety Monitor (LSM)

The overall role of the Local Safety Monitor (LSM), who is an experienced clinician based in Ouagadougou, will be to support the clinical investigators and to act as a link between the investigators and the DSMB.

The LSM’s role will include:

- Acting as the study volunteer’s advocate;
- Promptly communicating relevant safety information to the DSMB;
- Providing advice to the investigators on whether a set of clinical circumstances in a study warrants formal notification to the DSMB;
- Unblinding a subject if deemed necessary to allow for adequate treatment;
- Liaising closely with the chair of the DSMB throughout the course of the trial;
- Suspension of vaccination for a major safety concern pending discussion with the DSMB

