## Elimination criteria during the study

The following criteria should be checked at each visit subsequent to the first visit. If any become applicable during the study, it will not require withdrawal of the subject from the study but may determine a subject’s evaluability in the according-to-protocol (ATP) analysis.

- Administration of a vaccine not foreseen by the study protocol during the period starting from 30 days before Dose 1 and ending 30 days after Dose 3.
- Use of any investigational or non-registered product (drug or vaccine) other than the study vaccines during the study period.
- Administration of immunoglobulins and/or any blood products during the study period.
- Chronic administration (defined as more than 14 days) of immunosuppressants or other immune-modifying drugs during the study period (for corticosteroids, this will mean prednisone, or equivalent,  0.5 mg/kg/day. Inhaled and topical steroids are allowed).

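### The ATP safety cohort has exclusions that can follow from an adverse event, so its safety result can look cleaner than it should

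*Protocol*

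**What the plan says.** The protocol defines two populations for safety.

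- **Total Vaccinated Cohort (16.3.1.1).** Here "the total analysis of safety will include all subjects with at least one vaccine administration documented", grouped by the treatment actually given. Neither a code break nor an elimination criterion excludes a child.
- **ATP cohort for analysis of safety (16.3.1.2).** Among other conditions, this keeps only subjects "for whom the randomization code has not been broken except for when unblinding has been carried out by the DSMB for Safety Analysis" and "who have not received a vaccine not specified or forbidden in the protocol and for whom elimination criteria were not applied".

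Two other parts of the protocol determine what those conditions do in practice.

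- **Who breaks the code.** Under the heading on blinding and breaking the blind, if safety or a similar reason requires it, "the Local Safety Monitor in Ouagadougou as well as AMANET Central Safety will unblind the specific enrolled subject", and the investigators are not to learn the allocation. The Local Safety Monitor section lists as one of that person's tasks "Unblinding a subject if deemed necessary to allow for adequate treatment".
- **What counts as elimination.** Section 8.4 includes "Administration of immunoglobulins and/or any blood products during the study period" and chronic use (more than 14 days) of immunosuppressive or immune-modifying drugs. It adds that meeting a criterion does not require withdrawal but "may determine a subject’s evaluability in the according-to-protocol (ATP) analysis".

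**The concern.** A population for safety analysis should not select children on what happened to them after vaccination. Two of the ATP conditions can do that.

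The code-break condition excepts only the DSMB. The protocol gives individual unblinding for safety or treatment to two other parties, so the child whose event was grave enough to need it is excluded because of that event. Little is gained in return. Events recorded before the break were assessed blind, and the blinding section says the investigators do not learn the allocation even afterwards.

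The elimination condition can act in the same way when the blood product or the prolonged immunosuppressant was given to treat an adverse event.

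Safety is the primary objective, and the analysis at one month after dose 3 looks only at safety data to decide whether development proceeds. The sample size section justifies the arm size by the chance of seeing at least one affected MSP3 recipient. If a single event is what the design is built to detect, a population that can shed that one child matters more than it would in a large trial.

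**Working it through.** **1. The passages side by side**

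| Step | Source | Content |
|---|---|---|
| Who may unblind one child | Blinding section; Local Safety Monitor section | Local Safety Monitor; sponsor's central safety function |
| Why | Same | Safety, or to treat the child |
| Which unblinding is excepted | 16.3.1.2 | Only that by the DSMB for safety analysis |
| Result | | A child unblinded by either of the other two is outside the ATP safety cohort |
| Blood products, long immunosuppression | 8.4 with 16.3.1.2 | May put the child outside, once the criterion is applied |
| Still counted | 16.3.1.1; Safety monitoring reports section | Total Vaccinated Cohort; all SAEs in the DSMB reports |

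**2. The plan's own detection figures**

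Inputs from 16.2: 15 enrolled and 14 completing per MSP3 arm. The chance of at least one event is 1 − (1 − p)^14.

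- p = 15%: 1 − 0.85^14 = 0.897 (stated 90%)
- p = 11%: 1 − 0.89^14 = 0.804 (stated 80%)
- p = 19%: 1 − 0.81^14 = 0.948 (stated 95%)

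The stated figures reproduce. They assume that every child with an event is counted.

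**3. What one exclusion does**

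Take one arm of 15 in which the only event is in the child who is then excluded. Intervals are exact (Clopper-Pearson), 95%.

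- Total Vaccinated Cohort: 1/15 = 6.7%. Lower limit 1 − 0.975^(1/15) = 0.2%; upper limit 31.9% (the 0.975 quantile of Beta(2, 14)).
- ATP safety cohort: 0/14 = 0%. Upper limit 1 − 0.025^(1/14) = 23.2%.

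With two such children, 2/15 = 13.3% (1.7% to 40.5%) becomes 0/13 = 0% (upper limit 24.7%).

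**4. Sensitivity if the ATP cohort were read alone**

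Let q be the share of children with an event who are excluded because of it. The protocol gives no value, so q is an assumption shown over a range. The chance of at least one retained event is 1 − (1 − p(1 − q))^14.

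| q | p = 11% | p = 15% | p = 19% |
|---|---|---|---|
| 0 | 80.4% | 89.7% | 94.8% |
| 0.10 | 76.8% | 86.9% | 92.8% |
| 0.25 | 70.0% | 81.2% | 88.4% |
| 0.50 | 54.7% | 66.4% | 75.3% |

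The first row is also the result when the Total Vaccinated Cohort is used, since no child with an event is dropped from it.

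**The case against.** The strongest answer is that no event disappears. A reader might infer from 16.3.1.2 that a severe event can take a child out of the safety analysis altogether. The documents do not support that: the Total Vaccinated Cohort safety analysis has neither exclusion, the DSMB reports list all SAEs and withdrawals due to adverse events, and the suspension rules refer to no analysis cohort. This objection stands and limits the point to the ATP result.

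A reader might also infer that a blood product or a long immunosuppressant course removes a child automatically. Section 8.4 says only that such a criterion may determine evaluability. That also stands: this route is conditional, whereas the code-break rule carries no such softening. In addition, the protocol gives no rate of code breaks or of blood-product use, and an exclusion triggered after D84 cannot affect the Go/No-Go analysis done straight after that visit.

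A third inference would be that the two cohorts have equal status and either could be quoted for the Go/No-Go. The protocol does not say so. It foresees a formal reporting and analysis plan, which is not shown and may name the primary set. The lack of a named primary set is therefore not itself the defect.

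Finally, 1/15 against 0/14 is a constructed case. It needs the arm's only event to be in the excluded child, the two intervals overlap heavily, and the analysis is descriptive. All of that is fair. It bears on how often the problem would show, not on whether the rule depends on outcome.

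**Conclusion.** The point holds in a narrow form. As written, the ATP safety cohort excludes a child whose code is broken by the Local Safety Monitor or the sponsor's central safety function, and may exclude one who meets an elimination criterion because of how an event was treated. Either exclusion can result from the event that the cohort is meant to count.

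One exclusion can turn 6.7% (0.2% to 31.9%) into 0% (upper limit 23.2%) in an arm of 15, provided that the excluded child has the arm's only event. The likely number of such children cannot be derived from the protocol.

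Severity is minor. The Total Vaccinated Cohort analysis is planned alongside and would show the event, so the risk is a misleadingly clean ATP table rather than lost safety data.

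**What to change.** Change the wording of section 16.3:

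1. In 16.3.1.2, extend the code-break exception from the DSMB to any unblinding for safety or treatment by the Local Safety Monitor or the sponsor's central safety function.
2. For children who meet an elimination criterion through blood products or immunosuppressants, count events up to the elimination date, including the event that led to it.
3. State that the Total Vaccinated Cohort, as treated, is the primary set for safety and for the D84 Go/No-Go, and that the ATP safety analysis is supportive. If the analysis plan already says this, a cross-reference is enough.

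Keep the exclusions for other investigational products and for vaccines not foreseen by the protocol. Deleting the whole elimination condition would readmit those children and make it harder to attribute events to the study vaccine.

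The cost is a few sentences, with no change to data collection, to who may unblind, or to the care of any child.
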